## 2.0 PATIENT ELIGIBILITY

### Inclusion Criteria

Subjects must meet all of the inclusion criteria to participate in this study.

1. Patients with incurable malignancies with  $\geq 50\%$  2-year cancer-associated mortality (as estimated by two physician and where appropriate according to 2014 NCDB data in Figure 1). Diseases include, but are not limited to:

|                                        |                                                 |
|----------------------------------------|-------------------------------------------------|
| Ampullary carcinoma                    | Intrahepatic cholangiocarcinoma (IHCC)          |
| Appendiceal cancer                     | Melanoma                                        |
| Colorectal cancer (CRC)                | Non-KIT GIST (gastrointestinal stromal tumor)   |
| Extrahepatic cholangiocarcinoma (EHCC) | Non-small cell lung cancer (NSCLC)              |
| Esophageal adenocarcinoma              | Ovarian cancer                                  |
| Gallbladder cancer (GBCA)              | Pancreatic ductal adenocarcinoma (PDAC)         |
| Gastric adenocarcinoma                 | Sarcoma (high-grade)                            |
| Head and neck cancer                   | Small bowel adenocarcinoma (including duodenal) |
| Hepatocellular carcinoma (HCC)         | Triple-negative breast cancer (TNBC)            |
|                                        | Urothelial cancer                               |

\* Note: We will limit gastrointestinal malignancies to no more than 65% of the case mix.

2. Patients with cancer of unknown primary or a rare tumor (i.e., fewer than 15 cases per 100,000 per year) with no approved therapies. (Patients in this inclusion criteria must meet all other exclusion and inclusion criteria except inclusion criteria #1)
3. Patients with incurable malignancies, irrespective of 2-year mortality, who, in the opinion of the investigator have no treatment option expected to yield significant clinical benefit."
4. Patients must have at least one of the following for a diagnosis/disease status:
  - a. Unresectable disease
  - b. Metastatic disease
  - c. Medically unfit for surgical resection but with an expected survival of  $> 3$  months, ECOG  $< 2$  and NYHA status  $\leq$  II (refer to status definitions in tables below)
  - d. Disease where no conventional therapy leads to a survival benefit  $> 6$  months in the respective cohort and line of therapy for which the patient is otherwise eligible
  - e. Actionable alterations determined by FoundationOne™
5. Treatment naïve for his or her newly diagnosed malignancy for enrollment to Groups 1 or 2.
6. Status post 1 or more unmatched systemic therapy regimens for enrollment to Group 3.
7. Ability to understand and the willingness to sign a written informed consent.
8. Patients must have measurable disease for malignancies: defined as at least one lesion that can be accurately measured in at least one dimension (longest diameter to be recorded for non-nodal lesions and short axis for nodal lesions) as  $\geq 20$  mm with conventional techniques or as  $\geq 10$  mm with spiral CT scan, PET-CT, MRI, or calipers by clinical exam.
9. Age  $\geq 18$  years.

10. ECOG Performance Status 0-1.

| Grade | Description                                                                                                                                                |
|-------|------------------------------------------------------------------------------------------------------------------------------------------------------------|
| 0     | Fully active, able to carry on all pre-disease performance without restriction                                                                             |
| 1     | Restricted in physically strenuous activity but ambulatory and able to carry out work of a light or sedentary nature, e.g., light housework or office work |
| 2     | Ambulatory and capable of all self-care but unable to carry out any work activities. Up and about >50% of waking hours                                     |
| 3     | Capable of only limited self-care, confined to a bed or chair >50% of waking hours                                                                         |
| 4     | Completely disabled. Cannot carry on any self-care. Totally confined to bed or chair                                                                       |
| 5     | Dead                                                                                                                                                       |

11. New York Heart Association (NYHA) Functional Classification I-II.

| NYHA Class | Symptoms                                                                                                                                                   |
|------------|------------------------------------------------------------------------------------------------------------------------------------------------------------|
| I          | Cardiac disease, but no symptoms and no limitation in ordinary physical activity, e.g. shortness of breath when walking, climbing stairs etc.              |
| II         | Mild symptoms (mild shortness of breath and/or angina) and slight limitation during ordinary activity.                                                     |
| III        | Marked limitation in activity due to symptoms, even during less-than-ordinary activity, e.g. walking short distances (20–100 m). Comfortable only at rest. |
| IV         | Severe limitations. Experiences symptoms even while at rest . Mostly bedbound patients.                                                             |

12. Adequate organ and marrow function as defined below:

- Absolute neutrophil count  $\geq 1.5 \times 10^9/L$
- Platelet count  $\geq 100 \times 10^9/L$
- Total bilirubin  $\leq 2.0 \times$  institution's ULN
- Patients without underlying liver disease
  - ALT and AST  $\leq 2.5 \times$  institutional upper limit of normal
- Serum creatinine  $\leq 2.0 \times$  institution's ULN or 24-hour creatinine clearance  $\geq 50$  ml/min

13. At the time of treatment, patients should be off other anti-tumor agents for at least 5 half-lives of the agent or 3 weeks from the last day of treatment, whichever is shorter to enroll in Group 3. Patients must not have been treated with anti-tumor agents to enroll in Group 1 or Group 2. Patients must be off prior antibody therapy for at least 3 half-lives before starting treatment. Patients may enroll on study even while receiving treatment.

14. Able to swallow and retain oral medication if needed.

15. Patients must have evaluable tissue/blood for testing as specified by the concurrent FoundationOne™ criteria. This will be obtained during the standard of care tumor diagnosis and tumor staging evaluation.

16. Female patients of childbearing potential must have a negative serum pregnancy test and agree to use at least one form of pregnancy prevention during the study and for at least one month after treatment discontinuation. For the purposes of this study, child-bearing potential is defined as: all female patients that were not in post-menopause for at least one year or are surgically sterile (site-specific criteria applying to Avera only)
17. Male patients must use a form of barrier pregnancy prevention approved by the investigator / treating physician during the study and for at least one month after treatment discontinuation (site-specific criteria applying to Avera only).

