The current study will perform tumor molecular profiling through FoundationOne™ to navigate patients to a matched therapy at the discretion of their treating physician. For those patients with an actionable tumor alteration, matched therapy will be recommended by the Study Committee (or Molecular Tumor Board) from either FDA approved drugs or matched agents under investigation in a separate clinical trial. Those patients, for whom there are no available matched treatments, will serve as the unmatched therapy controls.

Patients with no actionable alterations by FoundationOne™ will be considered to have completed their participation in the study. Their basic data will be captured including demographics and tumor type and accounted into the denominator for feasibility analysis.

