### **Endpoints**

#### **Primary Endpoint:**

The proportion of patients who receive molecularly targeted matched treatment **after recommendations** based on genomic analysis

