#### **Secondary Endpoints:**

Determine the:

1. Proportion of patients that consent of all patients approached for the study
2. Time from informed consent to the receipt of FoundationOne™ genomic analysis
3. Proportion of patients with actionable genomic alteration
4. Proportion with insurance coverage for receiving molecularly targeted matched treatment based on genomic analysis

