### **Tumor Profiling**

Patients who meet the eligibility criteria and provide consent will have their tumor and/or blood profiled via Foundation Medicine's FoundationOne™ and/or FoundationACT™ assays. Available tissue/blood will constitute an adequate biopsy for molecular testing in the metastatic setting. If the patient has not had intercurrent targeted therapy, an archived diagnostic tumor sample will suffice. If the patient has received targeted therapy (Group 3), all attempts will be made to acquire a post-treatment biopsy.[7] Previous studies have shown that, in the absence of intercurrent targeted therapy, archival tissue is adequate for molecular testing and that matched treatment based on results from archival tissue is associated with significantly higher than expected response rates.[6, 8] If an eligible patient has had their tumor profiled via Foundation Medicine's FoundationOne™ assay under the auspices of routine clinical care, but they meet all criteria for enrollment to I-PREDICT, they may be consented and enrolled.

If the sample is not able to be tested or fails testing, additional sections will be sent to Foundation Medicine. If re-testing fails, a repeat biopsy may be performed if clinically appropriate or the patient may receive traditional chemotherapy. We will not delay beyond 6 weeks while awaiting Foundation Medicine testing.

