### **Patient Replacement**

Patients may be replaced if they have withdrawn from the study prior to having their tumor profiled in order to obtain 1150 evaluable patients with FoundationOne™ analyses.

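### Three entry and replacement rules can tilt the feasibility endpoints in the favourable direction, by an amount the protocol does not allow to be fixed

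*Protocol*

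**What the plan says.** **Endpoints.** The primary endpoint (Section 1.5) is "The proportion of patients who receive molecularly targeted matched treatment" following genomic recommendations; the denominator is not defined further. Section 5.1 calls the study feasible if at least 40% of patients (N ≥ 30) are matched in each group. Secondary endpoint 2 is "Time from informed consent to the receipt of FoundationOne" results, repeated in Section 6.5. Secondary endpoint 3 is the proportion with an actionable alteration.

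**Entry.** Criterion 4 in Section 2.1 reads "Patients must have at least one of the following for a diagnosis/disease status", and item 4e is "Actionable alterations determined by FoundationOne". Section 3.2 (Tumor Profiling) adds that a patient may come in after profiling "under the auspices of routine clinical care, but they meet all criteria for enrollment to I-PREDICT, they may be consented and enrolled".

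**Replacement.** Section 3.8: "Patients may be replaced if they have withdrawn from the study prior to having their tumor profiled in order to obtain 1150 evaluable patients" with assay results.

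**Text that points the other way.** Section 1.2 says of patients with no actionable alteration: "Their basic data will be captured including demographics and tumor type and accounted into the denominator for feasibility analysis". Section 3.2 (Study Groups) defines all three groups by unresectable, metastatic or medically unfit status together with treatment history. None is defined by a genomic result.

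**The concern.** The study asks how often, and how fast, testing leads to matched treatment. That needs a denominator fixed before the result is known and kept afterwards. Here a patient can enter with the result in hand, an endpoint result is itself an entry item, and a patient lost before the assay can be substituted. Loss before the result bears on feasibility: Section 1.4 makes it a secondary objective to learn whether physicians can wait for molecular information.

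At stake are the 40% success rule, the actionable proportion and the turnaround time. Where the rules have an effect, it is in the direction that makes the approach look more feasible.

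**Working it through.** **Inputs from the protocol.** 150 patients in Groups 1 and 2 together, 40% (30) in Arm A and 60% (45) in Arm B (Section 6.2); 50–70% expected to be actionable and about 40% of those matched (Section 3.2, Molecular Matching); success at 40% or more per group (Section 5.1).

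**Assumed, not in the protocol.** g, the share of patients profiled before consent; q, the actionable rate among them; w, the share of consented patients who withdraw before profiling.

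**1. The plan's own figure.** With equal groups, 150/2 = 75. Then 0.40 × 75 = 30 and 0.60 × 75 = 45, so the split reproduces.

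**2. Expectation without selection.** 0.50 × 0.40 = 20% and 0.70 × 0.40 = 28% matched, or 15 to 21 of 75. The binomial probability of at least 30 of 75 is 0.0001 to 0.017. On these rates 40% is expected only if every enrolled patient is actionable.

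**3. Pre-profiled patients and the two proportions.** With a the actionable rate in the other patients, the observed actionable share is gq + (1 − g)a. If q = a, it equals a and nothing shifts. The upper limit is q = 1, where only known positives are referred. The share is then g + (1 − g)a, and the matched share is 0.40 times that. Ranges run from a = 0.50 to a = 0.70:

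| g (assumed, with q = 1) | Actionable | Matched | P(≥ 30 of 75) |
|---|---|---|---|
| 0 | 50–70% | 20–28% | 0.0001–0.017 |
| 10% | 55–73% | 22–29% | 0.0003–0.029 |
| 25% | 62.5–77.5% | 25–31% | 0.003–0.062 |
| 50% | 75–85% | 30–34% | 0.041–0.165 |

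Example: 0.25 + 0.75 × 0.50 = 0.625, and 0.40 × 0.625 = 0.25. The true shift lies between zero and these values as q runs from a to 1.

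**4. Pre-profiled patients and turnaround.** This effect does not depend on q. If T is the mean among prospectively profiled patients and the others count as zero, the reported mean is (1 − g)T: 0.90T, 0.75T or 0.50T at g = 10%, 25% or 50%, and less if negative times are kept. No figure in days follows, because the protocol gives no expected consent-to-report time. The 14–17 days in Section 1.2 run from receipt of the sample.

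**5. Replacement.** If withdrawn patients leave the denominator, the share of consented patients is the evaluable share times (1 − w). An evaluable 40% is then 0.40 × 0.95 = 38%, 0.40 × 0.90 = 36% or 0.40 × 0.80 = 32% of consented patients at w = 5%, 10% or 20%. For 1150 evaluable patients, w = 10% means 1150/0.90, about 1278 consented and 128 withdrawn.

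**6. Item 4e.** Section 2.1 accepts an actionable result as a qualifying status. Section 1.5 makes that result an endpoint, Section 1.2 keeps patients without one in the denominator, and the groups in Section 3.2 have no place for a patient whose only qualifying item is 4e. Patients who do fit a group already meet 4a, 4b or 4c. So 4e is a contradiction in the text with little enrichment of its own.

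**The case against.** The strongest case against has five parts.

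- **Primary outcome.** A reader might infer that the primary denominator is selected on the outcome. It is not: the outcome is receipt of matched treatment, and actionability is only a precondition, which the protocol expects about 40% of actionable patients to convert. This stands.
- **Neutral wording.** The pre-profiling rule admits patients whatever their result, and patients without an actionable alteration stay in the denominator. Inflation of the two proportions therefore needs selective referral, which is plausible but not documented. This stands for the proportions. It does not touch turnaround.
- **Replacement.** It is optional, covers only withdrawal before profiling, and is worded as an accrual target. Removal from the denominator is implied by the word evaluable and never stated. A reader might infer that all patients who could not wait are discarded; the text does not go that far. What stands against the plan is that the denominator of its success rule is open to two readings.
- **Visibility and the SAP.** Section 6.5 reports the minimum, quartiles and a distribution plot, so zero or negative times would show. Showing them does not remove them from the mean and median. An SAP, which was not at hand, may define analysis sets, but the entry, replacement and success rules are fixed in the protocol.
- **Effect on the conclusion.** In step 3 the expected matched share stays below 40% even at g = 50%, and the analysis is declared descriptive. This stands and limits the weight of the point. The replacement reading still matters for a group truly near the threshold.

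**Conclusion.** The point holds in a limited form. Shortening of secondary endpoint 2 follows directly if patients profiled before consent are counted from consent, and grows with their share. Upward bias in the actionable and matched proportions is possible but conditional on preferential referral of known positives. It ranges from zero to the table values, which rest on an assumed 10–50% pre-profiled share, all of it actionable. The replacement rule, on its implied reading, lets a group with 36% or 32% of consented patients matched meet the 40% rule if 10% or 20% withdraw early; both rates are assumptions. Item 4e should be reconciled for consistency more than for its numerical effect.

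The direction follows from the rules, while the size cannot be fixed from the protocol. The effects should not simply be multiplied together, since a patient profiled before consent cannot withdraw before profiling.

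**What to change.** 1. State the primary denominator as all eligible consented patients in each group. Count withdrawal, death or test failure before a profile is obtained as not matched. Replacements may still be enrolled, but they do not remove the patient they replace.
2. Flag every patient whose report predates consent, whatever the result. Exclude these patients from secondary endpoint 2. Report secondary endpoint 3 and the primary endpoint separately for pre-profiled and prospectively profiled patients.
3. Split by report date against consent date, not by use of item 4e. Excluding only patients who qualified through 4e would remove positives alone and bias the actionable proportion downward.
4. Delete 4e as an entry item, or reconcile it with Sections 1.2, 1.5 and the group definitions in Section 3.2.

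The cost is denominator wording and one flag derived from the consent and report dates that secondary endpoint 2 already needs. No visit, sample or treatment changes. The downside is somewhat lower headline proportions and a longer reported turnaround.

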### **Tumor assessment**

Tumor imaging (or clinical exam when applicable) will be performed as part of standard of care. Imaging based evaluation should always be done rather than clinical examination unless the lesion(s) being followed cannot be imaged but are assessable by clinical exam. The same method of assessment and the same technique should be used to characterize each identified and reported lesion at baseline and during follow-up.

Patients will be considered evaluable for the study if they had their baseline scan within 30 days of the start of therapy. Tumor measurements will be assessed according to RECIST v1.1 (see Appendix A).

In addition, biochemical markers (tumor markers) may be considered as a secondary method for assessing tumor response.

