**1.1.1 Measurable**

*Tumor lesions:* must be accurately measured in at least one dimension (longest diameter in the plane of measurements is to be recorded) with a minimum size of:

4. 10 mm by CT scan (CT scan slice thickness no greater than 5 mm).
5. 10 mm caliper measurement by clinical exam (lesions which cannot be accurately measured with calipers should be recorded as non-measurable).
6. 20 mm by chest X-ray.

*Malignant lymph nodes:* to be considered pathologically enlarged and measurable, a lymph node must be  $\geq 15$  mm in *short* axis when assessed by CT scan. At baseline and in follow-up, only the *short* axis will be measured and followed.

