**1.1.2 Non-measurable**

All other lesions, including small lesions (longest diameter  $< 10$  mm or pathological lymph nodes with  $\geq 10$  to  $< 15$  mm short axis) as well as truly non-measurable lesions. Lesions considered truly non-measurable include: leptomeningeal disease, ascites, pleural or pericardial effusion, inflammatory breast disease, lymphangitic involvement of skin or lung, abdominal masses/abdominal organomegaly identified by physical exam that is not measurable by reproducible imaging techniques.

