## **2 Tumor Response Evaluation**

### **2.1 Baseline documentation of ‘target’ and ‘non-target’ lesions**

When more than one measurable lesion is present at baseline all lesions up to a maximum of five lesions total (and a maximum of two lesions per organ) representative of all involved organs should be identified as target lesions and will be recorded and measured at baseline (this means in instances where patients have only one or two organ sites involved a maximum of two and four lesions respectively will be recorded).

Target lesions should be selected on the basis of their size (lesions with the longest diameter), be representative of all involved organs, but in addition should be those that lend themselves to reproducible repeated measurements. It may be the case that, on occasion, the largest lesion does not lend itself to reproducible measurement in which circumstance the next largest lesion that can be measured reproducibly should be selected.

*Lymph nodes* merit special mention since they are normal anatomical structures that may be visible by imaging even if not involved by tumor. Pathological nodes that are defined as measurable and may be identified as target lesions must meet the criterion of a short axis of P15mm by CT scan. Only the short axis of these nodes will contribute to the baseline sum. The short axis of the node is the diameter normally used by radiologists to judge if a node is involved by solid tumor. Nodal size is normally reported as two dimensions in the plane in which the image is obtained (for CT scan this is almost always the axial plane; for MRI the plane of acquisition may be axial, sagittal or coronal). The smaller of these measures is the short axis.

For example, an abdominal node which is reported as being 20mm· 30mm has a short axis of 20mm and qualifies as a malignant, measurable node. In this example, 20mm should be recorded as the node measurement. All other pathological nodes (those with short axis P10mm but <15 mm) should be considered non-target lesions. Nodes that have a short axis <10mm are considered non-pathological and should not be recorded or followed.

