### **2.2.1 Evaluation of target lesions**

**Complete Response (CR):** Disappearance of all target lesions. Any pathological lymph nodes (whether target or non-target) must have reduction in short axis to <10 mm.

**Partial Response (PR):** At least a 30% decrease in the sum of diameters of target lesions, taking as reference the baseline sum diameters.

**Progressive Disease (PD):** At least a 20% increase in the sum of diameters of target lesions, taking as reference the smallest sum on study (this includes the baseline sum if that is the smallest on study). In addition to the relative increase of 20%, the sum must also demonstrate an absolute increase of at least 5 mm. (Note: the appearance of one or more new lesions is also considered progression).

**Stable Disease (SD):** Neither sufficient shrinkage to qualify for PR nor sufficient increase to qualify for PD, taking as reference the smallest sum diameters while on study.

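### Inclusion item 8 counts a 10 mm lymph node as measurable disease while Appendix A requires 15 mm, so a node-only patient can enter with no target lesion

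*Protocol*

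**What the plan says.** Item 8 of the Inclusion Criteria requires at least one accurately measurable lesion. For the dimension to be recorded it says: "longest diameter to be recorded for non-nodal lesions and short axis for nodal lesions". The size limit is 20 mm with conventional techniques, or 10 mm "mm with spiral CT scan, PET-CT, MRI, or calipers by clinical exam". Nodes are named, but no size of their own is given, so a node with a 10 mm short axis on CT satisfies the criterion.

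The Tumor assessment section makes Appendix A the measurement standard: "Tumor measurements will be assessed according to RECIST v1.1 (see Appendix A". Appendix A treats nodes differently in three places:

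- 1.1.1 Measurable: "to be considered pathologically enlarged and measurable, a lymph node must be" at least 15 mm in short axis on CT.
- 1.1.2 Non-measurable: the list that opens "All other lesions, including small lesions (longest diameter" includes nodes of 10 to under 15 mm short axis.
- 2.1 Baseline documentation: a node that may serve as a target lesion "must meet the criterion of a short axis of P15mm by CT scan", and "All other pathological nodes (those with short axis P10mm but <15 mm) should be considered non-target lesions". The letter P in both quotes is a lost sign for at least.

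**The concern.** The same 12 mm node is measurable at entry and non-measurable at response assessment. The purpose of item 8 is that every patient has something to measure. Appendix A 2.2.4 itself describes purely non-measurable disease as arising in trials that do not require measurable disease at entry. This trial does require it, yet such patients can still enter.

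Two exploratory endpoints depend on target lesions: regression rate, and the partial-response component of overall response rate (ORR). Both feed the comparisons in Section 6.6. The treatment text for Groups 1 and 2, Arm A, also sorts patients by changes in target lesions. Some eligible patients could therefore have no defined value on these measures, and sites could handle them differently.

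**Working it through.** The protocol states no figure for this point, so the check sets the rules side by side and adds some simple arithmetic.

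**Step 1. Where the two rules disagree.**

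| Nodal short axis on CT | Inclusion item 8 | Appendix A |
|---|---|---|
| under 10 mm | not measurable | non-pathological, not recorded |
| 10 to under 15 mm | measurable | non-measurable, non-target |
| 15 mm or more | measurable | measurable, may be a target |

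Only the middle row conflicts. It matters for a patient with no other lesion that meets Appendix A 1.1.1.

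**Step 2. What can be scored for that patient.**

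- Partial response (Appendix A 2.2.1): "At least a 30% decrease in the sum of diameters of target lesions, taking as reference the baseline sum diameters". With no target lesion there is no baseline sum. Appendix Table 2, for patients with non-target disease only, has no partial-response outcome.
- Regression rate (Exploratory Endpoints, item 2) is defined on target lesions only, so it has no value.
- Groups 1 and 2, Arm A: the First Response Assessment separates CR or PR from SD or PD, and a later step uses a decrease of 10-29% or under 10% in target lesions. Table 2 gives neither SD nor a percentage; its intermediate category is non-CR/non-PD. The passages do not cover this patient.
- Complete response, non-CR/non-PD and progression can all be scored under Table 2. PFS and OS therefore remain obtainable.

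**Step 3. How much ORR is affected.** ORR counts CR or PR. For non-target nodes, CR requires a short axis under 10 mm (Appendix A 2.2.3), with tumor markers normalized. For a single node of baseline size b, a 30% shrinkage leaves 0.70 × b. This is below 10 mm when b < 10/0.70 = 14.3 mm.

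- b = 12 mm: 0.70 × 12 = 8.4 mm, which meets the nodal CR size limit.
- b = 14.5 mm: 0.70 × 14.5 = 10.15 mm, which does not. Here a PR-sized shrinkage is lost.

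For a single node, then, a shrinkage of PR size fails to count on size grounds only between 14.3 mm and 15 mm. Some multi-node cases, and cases where markers stay raised, are further exceptions.

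In the other direction, the shrinkage needed to pass below 10 mm is anything more than (b − 10)/b. That is just above 0% from 10 mm, 2/12 = 16.7% from 12 mm and 4/14 = 28.6% from 14 mm. The low bar comes from Appendix A's own <10 mm rule, which is the same for target and non-target nodes.

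**Step 4. Weight of one patient, if responder status does change.** In the planned arms of 30 and 45, it is 1/30 = 3.3 and 1/45 = 2.2 percentage points. Section 6.2 allows up to 1000 patients in Group 3. At the protocol's 40/60 split that is 400 and 600, so 1/400 = 0.25 and 1/600 = 0.17 points.

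**The case against.** The strongest reply is that this is a wording mismatch with little consequence. Appendix A already provides for patients with only non-target disease through Table 2. ORR and regression rate are exploratory, and Section 6.3 calls the analysis exploratory and descriptive. The primary endpoint, the proportion receiving matched treatment, uses no imaging, and neither do the listed secondary endpoints. The affected patient must have incurable disease and no other lesion that Appendix A accepts, which should be uncommon. Restricting eligibility would also exclude patients who can still contribute to the primary endpoint.

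Most of this stands, and it limits the size of the problem. It does not remove the contradiction: no passage says which nodal limit applies, and Table 2 supplies neither a percent regression nor the categories used in the Arm A text.

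A reader might infer that ORR is distorted whichever way a site handles these nodes. The documents do not support that. CR stays scorable, and the <10 mm nodal limit is the same whether the node is called target or non-target. A reader might also take 3.3 or 2.2 points as the expected bias. Those figures hold only if a patient's responder status changes and the arms have 30 and 45 patients.

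**Conclusion.** The contradiction is real and stands in the protocol's own text. For a patient whose only qualifying disease is nodes of 10 to under 15 mm, percent regression is undefined, partial response cannot be scored, and the target-lesion cut-offs for Groups 1 and 2, Arm A, cannot be applied. The clearest loss is the regression rate.

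The effect on ORR is limited. The response-based suspension rule under Safety Stopping Rule is touched only through responder status, and nothing in the protocol shows that its result would change. The primary feasibility endpoint is unaffected, so it would be wrong to read this as a threat to the trial's main conclusion.

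The share of such patients is not given. That it is small is a judgement, not a figure from the protocol, and no effect on the stated 79% power can be calculated without assuming a share. It is worth correcting because one sentence would resolve it.

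**What to change.** Preferred: align item 8 with Appendix A 1.1.1, so that nodes qualify at a short axis of at least 15 mm on cross-sectional imaging and non-nodal lesions at a longest diameter of at least 10 mm. Cross-sectional imaging is better wording than CT alone, because the protocol also uses PET-CT and MR. The cost is one sentence and the exclusion of a few node-only patients.

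Alternative, if eligibility is to stay as it is: state that patients with no target lesion are scored by Appendix Table 2, count in ORR on that basis, and are left out of the regression-rate analysis, with their number reported by group and arm. This costs no patients, but regression rate then rests on a smaller set than ORR. The Arm A text for Groups 1 and 2 must also be reconciled with Table 2 for these patients; how is for the investigators to decide.

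A change to item 8 acts only on future enrolment. For anyone already entered under the present wording, the scoring rule and the count are needed in either case.
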